| Sample size considerations Anti-diabetic analyses  Sample sizes as per “feasibility counts” section, see table 1(below) for detectable differences in ethnic difference effect sizes. Corresponding to objective i), the proportion prescribed an anti-diabetic at 1 year post-diagnosis (42%) is taken from Sinclair et al (22) (detectable differences calculated using stpower cox command in Stata). Corresponding to objective ii), proportions prescribed metformin as first-line (73%) and a sulphonylurea as second line treatment (87%) are taken from Wilkinson et al (8) (power twoproportions command). Corresponding to objectives iv) and v), mean monitoring rate (2.45 times per year [extrapolated], assuming a SD of 2) (power twomeans command) and probability of treatment intensification at 1 year (24%) are taken from Khunti et al (23) (stpower cox command).  **Table 1. Detectable ethnic differences in outcomes.**   \| **Outcome** \| **Exposure (ethnicity): N vs. N** \| **Detectable ethnic difference effect sizes at α=0.05, β=0.90** \| \| --- \| --- \| --- \| \| Time from diagnosis to first anti-diabetic prescription \| South Asians vs. Europeans:  10.5K vs. 120.4K \| HR: 1.03 \| \| African Caribbeans vs. Europeans:  4.6K vs. 120.4K \| HR: 1.03 \| \| % prescribed metformin first-line \| South Asians vs. Europeans:  10.5K vs. 120.4K \| Difference in proportions: 1.4% \| \| African Caribbeans vs. Europeans:  4.6K vs. 120.4K \| Difference in proportions: 2.1% \| \| % prescribed sulphonylurea second-line \| South Asians vs. Europeans:  3.0K vs. 34.4K \| Difference in proportions: 2.0% \| \| African Caribbeans vs. Europeans:  1.3K vs. 34.4K \| Difference in proportions: 2.9% \| \| Mean monitoring rate, measurements per person year at risk \| South Asians vs. Europeans:  10.5K vs. 120.4K \| Rate difference: 0.07 \| \| African Caribbeans vs. Europeans:  4.6K vs. 120.4K \| Rate difference: 0.10 \| \| Time from sub-optimal diabetes control to treatment intensification \| South Asians vs. Europeans:  10.5K vs. 120.4K \| HR: 1.04 \| \| African Caribbeans vs. Europeans:  4.6K vs. 120.4K \| HR: 1.04 \| \| Time to antihypertensive initiation \| South Asians vs. Europeans:  7.6K vs. 119.4K \| HR: 1.02 \| \| African Caribbeans vs. Europeans:  3.8K vs. 119.4K \| HR: 1.02 \| \| Proportions of eligible people at high recorded CVD risk receiving statins \| South Asians vs. Europeans:  3K vs. 49K \| HR: 1.15 \| \| African Caribbeans vs. Europeans:  2K vs. 49K \| HR: 1.18 \|   Antihypertensive analyses  Sample sizes as per “feasibility counts” section. Little prior data exists in this area, but we can assume a mean time to measurement of 1 month (with an assumed SD of 1 month), as per guidelines for re-measurement after intensification (24). This would give a detectable ethnic difference in time until first monitoring as 0.04 months for South Asians vs. Europeans (using the power twomeans command in Stata), and 0.06 months for African Caribbeans vs. Europeans. Data from Petersen et al (25) suggest that 21% of those eligible for treatment for hypertension in the UK remain untreated. Adding this proportion to the expected numbers commencing antihypertensives by ethnicity (see feasibility count section), we would expect 119.4K Europeans, 7.6K South Asians and 3.8K African Caribbeans to be eligible for time to antihypertensive initiation analyses.  Lipid-lowering medication analyses  Sample sizes as per “feasibility counts” section. Assuming a mean time to monitoring of 3 months (26) and an SD of 1 month, the detectable ethnic difference in time until first monitoring would be 0.04 months for South Asians vs. Europeans, and 0.06 months for African Caribbeans vs. Europeans (using the power twomeans command in Stata). Chidwick et al reported that 24% of the high risk population received statins (21), equating to detectable ethnic differences in proportions receiving statins of HRs 1.18 and 1.15.  All detectable differences fall below what is likely to be considered clinically significant. |

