| O. Data/ Statistical Analysis For all parts of the study, the population will be people with and without new-onset type 2 diabetes active in CPRD from 2006 (see section K, above) and the exposure will be ethnicity (either South Asian vs. European [baseline] or African Caribbean vs. European [baseline], as detailed in section L, above). Covariates in base models will include age and sex, and further covariates will be considered individually, as outlined in section vi) below. Statistical analysis is further considered by objective:   1. **Outcome:** Proportion of those eligible for primary prevention who are prescribed a) antihypertensives and b) lipid-lowering medication   **Entry:** Date of incident a) hypertension Read code/ raised BP reading or b) elevated 10 year CVD risk score, at least 12 months after study start date of 1^st^ January 2005  **Exit:** First of; date of first antihypertensive/ lipid-lowering medication prescription (defined by the absence of a prescription for the medication in the previous 6 months’ records), end of study, leaving CPRD practice or death  **Analysis:** Proportions receiving antihypertensives/ statin will be compared by ethnicity, then logistic regression models will be used to adjust for confounding/ investigate potential mediators  **Example effect measure:** Odds ratio (OR) of receiving an antihypertensive/ lipid-lowering medication vs. not for each ethnic group of interest, stratified by time period since identification of hypertension/ elevated CVD risk   1. **Outcome**: time to initiation of first-line anti-diabetic/ antihypertensive/ statin, probability of receiving anti-diabetic/ antihypertensive/ statin at one year post-diagnosis/ identification of high CVD risk   **Entry**: date of type 2 diabetes diagnosis/ incident hypertension Read code or raised BP reading/ incident high 10 year CVD risk score recording  **Exit**: date of first anti-diabetic/ antihypertensive/ statin prescription (defined by the absence of a prescription for the medication in the previous 6 months’ records), or end of study/ leaving CPRD practice/ death  **Analysis**: summary statistics will be compared by ethnicity using Kaplan-Meier time-to-event analysis (cumulative failure probability in a given time frame by ethnicity, comparison of medians by log-rank test), Cox proportional hazards regression models will be used to adjust for confounding/ investigate potential mediators  **Example effect measure**: hazards ratio (HR) for anti-diabetic/ antihypertensive/ statin prescription   1. **Outcome:** proportions of patients prescribed medication from each anti-diabetic (stratified by first- to third-line treatment), antihypertensive and lipid-lowering class (defined by the absence of a prescription for the medication in the previous 6 months’ records)   **Sub-population:** a) all participants starting first- to third-line anti-diabetic treatment, b) all patients on antihypertensives, or c) all patients on lipid-lowering medication  **Analysis:** proportions receiving each drug will be compared by ethnicity, then logistic regression models will be used to adjust for confounding/ investigate potential mediators  **Example effect measures**: odds ratio (OR) of being prescribed metformin (=1) vs. non-metformin medication (=0) at first stage of treatment, OR of being prescribed sulphonylurea (=1) vs. non- sulphonylurea medication (=0) at second stage of treatment, OR of calcium-channel blocking antihypertensive prescription vs. non- calcium-channel blocking antihypertensive in those on antihypertensive treatment, OR of statin prescription vs. non-statin lipid-lowering medication prescription in those with >10% 10 year cardiovascular risk   1. **Outcome:** proportions of patients prescribed each dose of each anti-diabetic, antihypertensive and lipid-lowering medication, stratified by treatment stage (defined by the absence of a prescription for the medication in the previous 6 months’ records)   **Sub-population:** a) all participants on first- to third-line anti-diabetic treatment, b) all patients on antihypertensives, or c) all patients on lipid-lowering medication  **Analysis: :** proportions receiving each dose of each drug will be compared by ethnicity, then logistic regression models will be used to adjust for confounding/ investigate potential mediators  **Example effect measures**: OR of being prescribed maximum dose (2g daily) vs. sub-maximum dose of metformin, OR of being prescribed atorvastatin 10mg per day vs. higher doses (20mg, 40mg or 80mg)   1. **Outcome:** yearly monitoring rate post commencement of medication from each anti-diabetic (first- to third-line), antihypertensive and lipid-lowering class – i.e. number of times HbA1c/ blood pressure/ blood lipids measured per person-year of follow-up, stratified by year after commencement; may be multiple entry dates per person for different medications   **Entry:** first use of any medications of interest from 2006 onwards  **Exit:** first of; end of strata (e.g. 1 year after medication commencement), end of study/ leaving CPRD practice/ death  **Analysis:** summary statistics will be compared by ethnicity, Poisson regression modelling used to adjust for confounding/ investigate potential mediators  **Example effect measures**: yearly monitoring rate ratios (RRs)   1. **Outcome:** time to medication intensification (up-titration, addition or switching) after detection of sub-optimal control of diabetes, hypertension or blood lipids, or probability of intensification 1 year post-detection of sub-optimal control; may be multiple entry dates per person for different medications   **Entry:** date when sub-optimal risk factor control detected (see section M for how this is defined for each risk factor)  **Exit:** first of; date of anti-diabetic, antihypertensive or lipid-lowering treatment intensification, end of study/ leaving CPRD practice/ death  **Analysis:** summary statistics will be compared by ethnicity using Kaplan-Meier time-to-event analysis (cumulative failure probability in a given time frame by ethnicity, comparison by log-rank test), Cox proportional hazards regression models will be used to adjust for confounding/ investigate potential mediators  **Example effect measures**: cumulative failure probability for each ethnic group 1 year post detection of sub-optimal value, comparison of median survival times using the log-rank test by ethnicity, HRs of intensification stratified by year   1. **Outcome:** influence of deprivation, polypharmacy, multi-morbidity, drug adherence (iv) and v) only), patient engagement with healthcare, diabetes duration and HbA1c on any ethnic differences found in i) to v).   **Entry:** as above for i), iv) and v)  **Exit:** as above for i), iv) and v)  **Analysis:** as above for i) to v)  **Covariates:** smoking status, BMI, deprivation, polypharmacy, multi-morbidity, drug adherence, patient engagement with healthcare, diabetes duration and HbA1c  **Effect measures:** we will observe the degree of attenuation of the ethnic difference effect measure for each outcome when each covariate is inserted in turn to models, and thus evaluate the likelihood of confounding or mediation  Sub-group/ sensitivity analyses  See section O of original application  Plans for addressing misclassification and bias  See section O of original application  Multiple comparisons  See section O of original application |

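### One-year probabilities of starting or intensifying treatment are estimated by Kaplan-Meier with death as ordinary censoring, so they slightly overstate the share of patients actually treated

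*Supplement*

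**What the plan says.** The current text is section O (Data/Statistical Analysis) of the December 2019 amendment.

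- **Time to initiation (objective 2).** The outcomes include the "probability of receiving anti-diabetic/ antihypertensive/ statin at one year post-diagnosis/ identification of high CVD risk". Follow-up ends at the first prescription "or end of study/ leaving CPRD practice/ death". The summary is by Kaplan-Meier, giving the "cumulative failure probability in a given time frame by ethnicity", with a log-rank test.
- **Time to intensification (objective 6).** Follow-up ends at the first of "treatment intensification, end of study/ leaving CPRD practice/ death". An example effect measure is the "cumulative failure probability for each ethnic group 1 year post detection of sub-optimal value".
- **Adjusted analysis, both objectives.** "Cox proportional hazards regression models will be used to adjust for confounding/ investigate potential mediators".

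No event other than the prescription or the intensification is defined, so death can enter only as a censoring time. Nothing in the amendment or the original application mentions competing risks or cumulative incidence. Neither the bias section of the original application, which the amendment carries forward by reference, nor the original's limitations section raises death.

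**The concern.** Censoring in Kaplan-Meier means that the patient could still have the event later, at the same rate as those still followed. That is a reasonable working assumption for end of study, and perhaps for leaving the practice. It cannot describe a patient who has died untreated. With death censored, 1 minus Kaplan-Meier estimates the probability of treatment in a hypothetical population where nobody dies first. The plan's wording is about receiving treatment, and readers will take the figures as the share of patients treated by one year.

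The absolute level is therefore too high in each ethnic group. The difference between groups, read as a difference in the proportion treated, may also be off if the groups differ in mortality or in treatment rate. The plan says that it will attend to clinically meaningful effect sizes rather than p values, so its absolute probabilities should estimate what they are called.

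**Working it through.** **Inputs.** The sample size section of the amendment gives 42% prescribed an anti-diabetic at 1 year and 24% intensified at 1 year. Table 1 gives 10.5K South Asians and 4.6K African Caribbeans, each against 120.4K Europeans. Mortality is not in the documents; I assume 1-5% per year. I also assume constant hazards, and read the 42% and 24% as 1 minus Kaplan-Meier. The plan states no cumulative probability of its own by either estimator, so there is no figure to reproduce first.

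**Formulas.** With treatment hazard λ and death hazard μ:

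- Kaplan-Meier target: 1 − exp(−λt)
- Proportion actually treated by t: λ/(λ+μ) × [1 − exp(−(λ+μ)t)]

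λ = −ln(1 − 0.42) = 0.5447 per year for initiation, and −ln(1 − 0.24) = 0.2744 for intensification.

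**Worked case.** Initiation, μ = 0.02, t = 1: 0.5447/0.5647 × [1 − exp(−0.5647)] = 41.62%, against 42.00%. The excess is 0.38 points.

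**Overstatement (1 minus Kaplan-Meier less proportion treated), in points:**

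| Outcome | Horizon | 1 − KM | μ = 1% | μ = 2% | μ = 4% | μ = 5% |
|---|---|---|---|---|---|---|
| Initiation | 1 year | 42.0% | 0.19 | 0.38 | 0.75 | 0.94 |
| Intensification | 1 year | 24.0% | 0.11 | 0.23 | 0.45 | 0.56 |
| Initiation | 5 years | 93.4% | 1.37 | 2.71 | 5.28 | 6.53 |
| Intensification | 5 years | 74.6% | 1.43 | 2.82 | 5.48 | 6.76 |

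A simulation of 2 million patients for one-year initiation gave 41.82% treated at 1% mortality and 41.41% at 3%, against 41.81% and 41.43% from the formula.

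**Between groups, equal treatment hazards.** Suppose mortality is 2% in one group and 1% in the other, or 4% and 2%. Kaplan-Meier has the same target in both groups (42.0% and 42.0%; 24.0% and 24.0%). The proportions actually treated at 1 year are:

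- Initiation: 41.62% v 41.81% (0.19 points), or 41.25% v 41.62% (0.37 points).
- Intensification: 23.77% v 23.89% (0.11 points before rounding), or 23.55% v 23.77% (0.22 points).

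At 5 years the same assumptions give 1.3-2.6 points for initiation and 1.4-2.7 for intensification.

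**Scale.** The standard error of a one-year difference is about √[p(1−p)(1/n₁ + 1/n₀)]. For initiation it is 0.50 points (South Asian) and 0.74 (African Caribbean); for intensification, 0.43 and 0.64. Every one-year gap above is below one standard error.

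**Between groups, unequal treatment hazards.** A group with 42% initiation and 2% mortality has an excess of 0.38 points at 1 year. One with 24% and 2.5% mortality has 0.28. The excess depends on the treatment hazard as well as on mortality.

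**The case against.** The strongest reply is that the aim is ethnic differences in prescribing, and that a curve which sets mortality aside is a legitimate target for that. A reader might infer that Kaplan-Meier creates a spurious ethnic gap. It does not: with equal treatment hazards it shows none, and it is the cumulative incidence that differs, because of mortality. That part of the reply stands. It does not rescue the label, since the plan names the probability of receiving treatment and does not say that it means the probability were nobody to die.

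Other points on that side:

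- The original application stratifies analyses by age group, and the amendment keeps this. It should narrow mortality differences between ethnic groups. It leaves the overstatement within each stratum.
- One year is the only horizon named, and the error there is small. The 5-year figures need a longer time frame, which the wording permits but does not promise, and they extrapolate a constant hazard.
- The Kaplan-Meier results are summary statistics, and adjusted inference rests on Cox models. With death censored these give cause-specific hazard ratios, which are sound, as are the log-rank tests.
- Objective 1 separately reports proportions treated for antihypertensive and lipid-lowering drugs. It does not cover anti-diabetic initiation or any intensification.

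**Conclusion.** The point holds as a mismatch between a named outcome and its estimator. The stated probabilities of initiation and intensification will be too high in every group whenever mortality is above zero. Under constant hazards and an assumed 1-5% annual mortality, the one-year excess is about 0.2-0.9 points for initiation and 0.1-0.6 for intensification, rising to several points at 5 years if such horizons are reported.

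Two further readings go beyond the documents. One is that the overstatement is always greater in the group with higher mortality. That follows when treatment hazards are equal, but the order can reverse when they are not, and the documents do not show which group has the higher mortality. The other is that the distortion rivals the differences the study says it can detect. At 1 year, Table 1's HR of 1.03 for initiation corresponds to 0.94 points (42.94% against 42.00%) and HR 1.04 for intensification to 0.83 (24.83% against 24.00%). The gaps of 0.19-0.37 and 0.11-0.22 points are roughly 20-40% and 14-27% of these, and they rest on mortality assumed to be twice as high in one group as in the other.

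This is worth correcting because it is cheap and the outcome is named, but the consequence at one year is small.

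**What to change.** In section O, objectives 2 and 6, state that the cumulative probability of prescription or intensification will be estimated by the Aalen-Johansen cumulative incidence function with death as a competing event, and reported by ethnicity with 95% confidence intervals. Keep end of study and leaving the practice as censoring. Keep the cause-specific Cox hazard ratios as the measure of ethnic differences in prescribing.

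The cost is one sentence and a change of estimator in standard software. Death is already recorded as an exit, so no new data are needed. The stated treatment probabilities become slightly lower. Differences in cumulative incidence also reflect mortality, so they should be read beside the hazard ratios and not in place of them.

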| Objectives, Specific Aims and Rationale Overall aim  To investigate ethnic differences in prescribing for type 2 diabetes in UK primary care.  Objectives  For people of European, South Asian and African Caribbean origin, ethnic differences in the following will be investigated:   1. Proportions of people with: a) incident hypertension started on antihypertensives and b) an elevated 10 year CVD risk score (according to QRISK, ASSIGN, JBS2, Framingham or unspecified risk-estimating equations (26)) being commenced on statin treatment. 2. Time to initiation of first-line anti-diabetic/ antihypertensive/lipid-lowering medication 3. Choice of anti-diabetic (first- to third-line), antihypertensive and lipid-lowering medication 4. Doses used for each anti-diabetic, antihypertensive and lipid-lowering medication 5. Monitoring rate after medication commencement 6. Time to medication intensification (up-titration, addition or switching) after detection of sub-optimal control of diabetes, hypertension or blood lipids   Additionally, we will examine potential confounding or mediating role/s of:   1. Smoking, BMI, deprivation, polypharmacy, multi-morbidity, drug adherence (for objectives v) and vi)), patient engagement with healthcare, diabetes duration and HbA1c (in people with diabetes).   Null hypotheses   1. No ethnic difference in proportions of people started on a) antihypertensives or b) statin treatment will be detected. 2. No ethnic difference in time to initiation of first-line anti-diabetic, antihypertensive or lipid-lowering medication will be detected. 3. Regarding choice of medication: 4. No ethnic difference in the proportions of people prescribed metformin as first-line, or sulphonylureas, DPP4-inhibitors, thiazolidinediones, SGLT2 inhibitors, GLP1 agonists or insulin as second- or third-line diabetes treatment will be observed. 5. No ethnic difference in the proportions of people prescribed ACE inhibitors/ angiotensin-receptor blockers, calcium-channel blockers or thiazide diuretics for hypertension will be observed. 6. No ethnic difference in the proportions of people with ≥10% cardiovascular disease risk who are prescribed lipid-lowering medication will be observed. 7. No ethnic difference in the proportions prescribed the maximum dose of anti-diabetic, antihypertensive or lipid-lowering medication will be observed, and the modal dose for each class will not differ by ethnicity. 8. No ethnic difference in the monitoring rates of anti-diabetic, antihypertensive or lipid-lowering medication will be observed. 9. No ethnic difference in time to treatment intensification (after the detection of sub-optimal control) of anti-diabetic, antihypertensive or lipid-lowering medication will be observed. 10. Associations between ethnicity and prescribing will not be confounded or mediated by smoking, BMI, deprivation, polypharmacy, multi-morbidity, drug adherence, patient engagement, diabetes duration or HbA1c (in people with diabetes).   Rationale  Research indicates that control of diabetes and its allied cardiovascular risk factors is poorer in UK’s minority ethnic groups than in the background white population. Crucially, these discrepancies are likely to contribute to higher rates of heart disease and stroke, in people with and without diabetes, seen in these groups. By examining the associations above, this study seeks to determine whether ethnic differences in prescribing for people with and without diabetes are present, and explanations for them.  It is important to compare prescribing in people with and without diabetes for each ethnic group. Our previous work suggests that diabetes is a much more potent CVD risk factor in people of South Asian and African Caribbean-origin than those of European-origin, and differential prescribing of statins and anti-hypertensives in those with vs. without diabetes is a possible explanation for this.  If ethnic inequalities in prescribing are present, their identification may influence future prescribing recommendations and thus eventually lessen the personal and societal burden of diabetes and cardiovascular disease complications in ethnic minority groups. |

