| Study Background The UK’s largest ethnic minority groups, people of South Asian and African Caribbean descent, are disproportionately affected by type 2 diabetes (1), and most types of cardiovascular disease (2). UKPDS (UK Prospective Study of Diabetes) established the importance of tight blood glucose control in reducing CVD complications (3), but research suggests that glucose control is poorer in UK South Asians and African Caribbeans than Europeans (4, 5), despite their greater prevalence of complications (2). Yet the use of anti-diabetic medication in these groups remains understudied. Blood pressure and lipid control is key in reducing CVD risk in people with and without diabetes (6), therefore we will also examine prescribing patterns for antihypertensives and lipid-lowering medication.  UK guidelines recommend metformin as first-line anti-diabetic therapy, with several choices of further agents before insulin use (7). A recent study has reported on the choice of second-line treatments in CPRD (8; ISAC protocol number 16_267), with some indication that people from ethnic minority groups are less likely to receive newer anti-diabetic drugs. However, the influence of key factors such as diabetes duration and adherence to treatment were not accounted for, and the related questions of monitoring frequency and expediency of appropriate treatment intensification were not studied. Moreover, evidence from smaller primary care databases suggests South Asians and African Caribbeans are less likely than Europeans to receive insulin, and more likely to be on a higher number of oral diabetes drugs (5, 9). UK hypertension guidelines advocate calcium-channel blockers (CCBs) as first-line treatment for African Caribbeans, and ethnic differences in monotherapy are established (10), but little examination of ethnic differences in prescribing exists beyond this. Studies from aggregated primary care data indicate that statins may be under-prescribed in areas with large ethnic minority populations (11, 12), but were limited by analysis at area level.  Delay in anti-diabetic treatment intensification is linked to poorer subsequent control (13), but in spite of the poorer diabetic control in ethnic minority groups, ethnic differences in time to intensification have never been studied. Equally, an absence of research on ethnic differences in intensification of antihypertensives exists (14). However, previous research indicates that African Caribbean people are less likely than their white counterparts to be prescribed statins (15), though it is unclear if this is the case for people with diabetes. Additionally, whilst evidence from CPRD indicates that hypercholesterolaemia with high cardiovascular risk is inadequately treated in people with diabetes (16), scrutiny by ethnicity is lacking. |

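### Antihypertensive choice is pooled over treatment lines and so cannot address the stated gap beyond monotherapy; the lipid choice null is set in a population where it cannot vary

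*Supplement*

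**What the plan says.** All references are to the Supplement, amendment of 9 December 2019, unless stated.

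**Choice outcome (section O).** The outcome is "proportions of patients prescribed medication from each anti-diabetic (stratified by first- to third-line treatment), antihypertensive and lipid-lowering class", with new use "defined by the absence of a prescription for the medication in the previous 6 months’ records". Treatment line is attached to anti-diabetics only. The sub-populations for the other two drug groups are "b) all patients on antihypertensives, or c) all patients on lipid-lowering medication". The example effects are "OR of calcium-channel blocking antihypertensive prescription vs. non- calcium-channel blocking antihypertensive in those on antihypertensive treatment" and "OR of statin prescription vs. non-statin lipid-lowering medication prescription in those with >10% 10 year cardiovascular risk".

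**Null hypotheses (Objectives section).** For antihypertensives: "No ethnic difference in the proportions of people prescribed ACE inhibitors/ angiotensin-receptor blockers, calcium-channel blockers or thiazide diuretics for hypertension will be observed". No line is named. For lipids: "No ethnic difference in the proportions of people with ≥10% cardiovascular disease risk who are prescribed lipid-lowering medication will be observed".

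**Study Background.** It notes that UK guidance favours CCBs as first-line treatment for African Caribbeans. It adds that "ethnic differences in monotherapy are established (10), but little examination of ethnic differences in prescribing exists beyond this".

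**Objective 1 (sections L and O).** The amendment adds a logistic comparison of prescribed against not prescribed among people eligible for primary prevention. Section L sets lipid eligibility at a recorded risk of at least 20% for 2006–2013 and at least 10% for 2014–2019, to follow guideline changes. That rule sits in the paragraph on people without diabetes.

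**The concern.** The Background treats the first-line ethnic difference in antihypertensive class as known and guideline-directed, and places the gap beyond it. A CCB contrast pooled over everyone on treatment includes that known difference. It is also sensitive to how far along treatment each group is. If the null is rejected for African Caribbeans, the reader cannot tell guideline-concordant first-line prescribing from a difference in add-on choice. The Rationale nevertheless speaks of identifying ethnic inequalities in prescribing.

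The lipid null has a different fault. It asks who receives a lipid-lowering drug, but its analysis set contains only people who already receive one. Under-prescribing would show among the untreated, and they are left out. Statin against non-statin is a legitimate question, but it is not the one the null states.

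**Working it through.** **1. The plan's own denominators.** The Feasibility counts give 120.4K Europeans, 10.5K South Asians and 4.6K African Caribbeans starting first-line anti-diabetic treatment, with 77% on antihypertensives and 64% on statins.
- × 0.77: 92.7K / 8.1K / 3.5K, as stated.
- × 0.64: 77.1K / 6.7K / 2.9K, as stated.

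These counts reproduce. The plan states no detectable difference for antihypertensive or lipid choice, so there is no power figure to check here.

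**2. Does any analysis isolate later-line antihypertensive class?**
- Choice outcome: line is given for anti-diabetics only.
- Six-month rule: it identifies a newly used drug, not the line at which it was added.
- Dose outcome: stratified by treatment stage, but it concerns dose within a drug, not class.
- Intensification: time to any up-titration, addition or switch, not which class is chosen.
- General stratification (original application, carried over by the amendment): age group and calendar time.

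None of them isolates it.

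**3. Effect of pooling lines (all inputs assumed).** Pooled proportion = Σ (share at line × CCB use at that line). Give both groups the same CCB use of 30% / 60% / 85% at lines one to three, so each within-line odds ratio is 1.
- Europeans, mix 50/30/20: 0.150 + 0.180 + 0.170 = 0.500.
- Comparison group with more later-line patients, 35/35/30: 0.105 + 0.210 + 0.255 = 0.570. OR = (0.570/0.430)/(0.500/0.500) = 1.33.
- Comparison group with fewer, 60/27/13: 0.180 + 0.162 + 0.1105 = 0.4525. OR = (0.4525/0.5475)/1 = 0.83.

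With CCB use by line of 40/60/80% or 30/50/70%, and an intermediate mix of 42/33/25, the results lie between these limits. This shows the treatment-stage mechanism only. A true first-line difference would add to it.

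**4. Lipid denominator.** In the choice sub-population the proportion prescribed a lipid-lowering drug is 100% in every ethnic group, so the null's quantity cannot differ. The Sample size section takes 24% of high-risk people as receiving statins. Conditioning on statin treatment would keep 0.24 × 49K = 11.8K Europeans, 0.24 × 3K = 0.72K South Asians and 0.24 × 2K = 0.48K African Caribbeans, and drop 76%. If a minority group's uptake were 20% (assumed) against 24%, the uptake odds ratio would be (0.20/0.80)/(0.24/0.76) = 0.79. With equal statin shares among the treated (assumed), the statin against non-statin odds ratio would still be 1.00. Uptake of 22% or 28% gives uptake odds ratios of 0.89 and 1.23, again with 1.00 among the treated.

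**5. Why splitting by line is not enough alone (inputs assumed).** Let 30% of Europeans and 70% of African Caribbeans start on a CCB. Let everyone progress, and let half of those not on a CCB add one, whatever their ethnicity. Second-line CCB starts are 0.5 × 0.70 = 35% and 0.5 × 0.30 = 15%. OR = (0.15/0.85)/(0.35/0.65) = 0.33, with no difference in prescribing given prior class. An unconditioned later-line contrast therefore carries the first-line difference forward with its sign reversed.

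**The case against.** The strongest reply is that the antihypertensive null names no line, so a comparison over all treated patients answers it as written. That stands. A reader might infer that neither analysis can answer its question, and for antihypertensives the documents do not support so much. What the pooled contrast cannot do is serve the gap in the Background.

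It is also fair that the dose outcome is staged while using the same sub-population wording, so that wording does not rule out staging. Intensification, another gap named in the Background, has its own objective. The authors state the guideline openly and put clinically meaningful effect sizes ahead of p values. All this tempers the harm, but none of it supplies a later-line class contrast.

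A reader might also infer that the African Caribbean null is bound to be rejected, or try to size the distortion. For example, first-line CCB use of 30% against 70%, 50% in both groups later, and half of starts first-line give pooled 40% against 60%, OR 2.25. No document supplies those inputs. They also fail if line is counted by new-class starts: with 70% already on a CCB and equal progression, at most 30% can newly start one later. The supportable statement is that the null may be rejected because of the guideline.

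For lipids, objective 1 already compares treated with untreated eligible people, so it would be wrong to infer that uptake goes untested. The thresholds by calendar period are deliberate. What remains is a null placed under the wrong objective, a mismatch with the 2006–2013 threshold, and no stated lipid eligibility for people with diabetes.

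**Conclusion.** The point holds in two limited parts.

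First, antihypertensive class choice is pooled over lines, and no other planned analysis isolates later-line class. The pooled odds ratio answers the literal null but not the question the Background leaves open, and its cause would be ambiguous for African Caribbeans. No comparable first-line guidance is cited for South Asians, so for them the argument rests on treatment stage alone. The 0.83 to 1.33 range illustrates direction and rough scale; it rests on assumed line mixes and CCB use and is not a forecast.

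Second, the lipid choice null cannot be tested in its own sub-population. This follows from the definitions and needs no assumption. Objective 1 answers most of the uptake question. It leaves uncovered people with a recorded risk of at least 10% but below 20% in 2006–2013, and it does not define eligibility for people with diabetes, although the Background says it is unclear whether lower statin prescribing to African Caribbeans extends to them.

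Both parts should be corrected before analysis. Neither undermines the study as a whole.

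**What to change.** **Antihypertensives.** Extend the line stratification in the choice outcome to antihypertensives (first, second and third added class). Make the second- and third-line ethnic contrasts within, or adjusted for, the classes already prescribed. Name these contrasts as the answer to the gap beyond monotherapy, and keep the pooled odds ratio as description.

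**Lipids.** Move the uptake null to objective 1, with treated and untreated eligible people as the denominator. Reconcile the null's 10% with the calendar-period thresholds in section L, and state the eligible population for people with diabetes. Under the choice objective, reword the lipid null as statin against non-statin among the treated.

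**Cost.** This is plan wording and extra strata on data already requested. The loss is precision at later lines for African Caribbeans, who number about 3.5K with diabetes and 3K without before any split. If 20% were at third line (assumed), that leaves about 0.7K and 0.6K, fewer still within prior-class strata, so those contrasts should be reported as estimates with intervals.
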